## Abstract

**Background:**

Multidrug-resistant Gram-negative bacterial (MRGNB) infections represent a major public health threat. Cancer patients and, among them, hematological patients are most vulnerable to these infections. Gut colonization by MRGNB is a common phenomenon occurring during hospitalization and chemotherapy exposure. In the neutropenic phase that occurs after chemotherapy, MRGNB translocation occurs increasing patient’s mortality. Fluoroquinolone prophylaxis with ciprofloxacin or levofloxacin efficacy is now being questioned due to the increase of incidence in MRGNB.

**Methods:**

A phase III randomized, controlled, clinical trial, open-label parallel-group with a 1:1 ratio, aimed to demonstrate the non-inferiority of oral fosfomycin versus oral ciprofloxacin for febrile neutropenia prevention in patients with acute leukemia (AL) or hematopoietic cell transplant (HSC) receptors. Weekly surveillance cultures are planned to detect gut colonization. Changes in fecal microbiome at the beginning and end of prophylaxis will also be analyzed.

**Discussion:**

This trial will provide evidence of the efficacy of an alternative drug to ciprofloxacin for febrile neutropenia prevention in high-risk hematological patients. The battery of planned microbiological studies will allow us to evaluate prospectively the microbiological safety of both pharmacological strategies in terms of the selection of MRGNB occurring in each arm. In addition, valuable information on the way in which each drug changes the fecal microbiome of the patients throughout the treatment will be generated.

**Trial registration:**

Clinical trials NCT05311254, Registered on 5 April 2022, https://clinicaltrials.gov/ct2/show/NCT05311254?term=FOVOCIP&cntry=ES&draw=2&rank=1. Protocol version: 3.0, dated 20 May 2022.

## Administrative information

Note: the numbers in curly brackets in this protocol refer to SPIRIT checklist item numbers. The order of the items has been modified to group similar items (see http://www.equator-network.org/reporting-guidelines/spirit-2013-statement-defining-standard-protocol-items-for-clinical-trials/).

## Introduction

### Background and rationale {6a}

The use of fluoroquinolones (FQ) ciprofloxacin or levofloxacin is an established practice for the prevention of infectious events in hematologic patients in whom long lasting and profound neutropenia (absolute neutropenia count ≤ 0.1/ × 10^9^/L for more than 7 days) is expected. Patients included in this category are acute leukemia (AL) patients treated with intensive chemotherapy and allogeneic hematopoietic stem cell transplant (HSCT) recipients [1, 2]. In these patients, FQ exposure is associated with the development of multidrug-resistant Gram-negative bacteria (MRGNB) gut colonization [3]. These infections are associated with increased mortality in HSCT receptors and AL patients [4, 5]. A way of limiting the spread of MRGNB is by means of systematic surveillance of gut colonization by these bacteria. This practice has shown to prevent nosocomial dissemination by carbapenemase-producing enterobacteria [6]. In hematological patients, systematic surveillance cultures are being increasingly performed because they also provide valuable information for adjusting antimicrobial therapy at the time of febrile neutropenia [7, 8].

The concerns about the increasing incidence of MRGNB and its risks have led to questioning the actual recommendation of FQ prophylaxis, especially in those settings with a baseline resistance rate above 20% [9]. However, it should be noted that no controlled clinical trial has supported abandoning prophylaxis. Moreover, leaving the decision of FQ prophylaxis to physician’s criteria puts the patients at risk of not receiving an adequate treatment.

In addition to multidrug resistance associated to FQ, musculoskeletal and neurological adverse events (AEs) related to them represent another problem. For this reason, the European Pharmacovigilance Risk Assessment Committee recommends restricting their use (https://www.aemps.gob.es/informa/notasinformativas/medicamentosusohumano-3/seguridad-1/2018/ni_muh_fv-14-2018-quinolonas-fluoroquinolonas/).

Finally, another aspect for which FQ may adversely impact the outcome of patients is the modification of the intestinal microbiota. It has been demonstrated that replacement of the normal fecal microbiota with an abnormal one occurs in patients undergoing allogeneic HSCT [10]. Among other factors, this event is the consequence of the exposure to antimicrobials, but it is also influenced by the occurrence of graft-versus-host disease. The available evidence is still insufficient, since other factors such as immunomodulatory therapies, types of transplantation (autologous versus allogeneic), chemotherapy, and even the state of the neoplasm (active versus remission) should be analyzed. Furthermore, it has also been documented that the intestinal microbiota is related to the development of infections in patients with AL, showing that those patients with low α-diversity have a higher risk of developing them [11].

All the aforementioned limitations related to FQ prophylaxis have pointed to the urgent need for exploring new prophylactic drugs. In the past decades, other drugs were evaluated without positive results. This is the case of cephalosporins [12] or cotrimoxazole, which was abandoned due to myelotoxicity and lack of activity against *P. aeruginosa* [13].

Fosfomycin is a broad-spectrum bactericidal antibiotic approved for the treatment of uncomplicated urinary tract infections, gastrointestinal tract infections, and dermatological infections caused by microorganisms sensitive to this antibiotic. It has activity against Gram-positive and Gram-negative microorganisms and against extended-spectrum B-lactamase *Enterobacteriaceae* (ESBL) and/or carbapenemase-producing strains of enterobacteria and multidrug-resistant *P. aeruginosa*, which makes its use attractive even in endemic settings [14].

In view of the above, the need of conducting this study is justified. The results could demonstrate the non-inferiority of oral fosfomycin compared to oral ciprofloxacin in preventing infections in patients with neutropenia at high risk of developing infection as well as its effect on the intestinal flora as assessed by surveillance cultures and fecal microbiota analysis.

### Choice of comparator {6b}

The choice of ciprofloxacin over levofloxacin is based on the evidence supporting its superiority in the prevention of febrile neutropenia [2] and the extensive experience accumulated with its use over two decades in this setting.

### Objectives {7}

#### Hypotheses

The use of oral fosfomycin is not inferior to oral ciprofloxacin in the prevention of fever of infectious origin in high-risk neutropenic patients. This hypothesis is based not only on the broad-spectrum activity of fosfomycin but also on the low rate of resistance to this drug. In addition, we anticipate that the clinical efficacy of fosfomycin will be accompanied by an acceptable safety profile. Thus, there is potential for fosfomycin to be useful as a prophylactic agent in settings endemic for GNMRB.

#### Objective

The main objective of this clinical trial is to demonstrate non-inferiority in efficacy of oral fosfomycin versus oral ciprofloxacin in preventing febrile neutropenia in patients with acute leukemia treated with intensive chemotherapy and/or recipients of hematopoietic stem cell transplantation.

### Trial design {8}

The FOVOCIP study is a randomized, open-label, phase III clinical trial with a non-inferiority design, in which patients are randomized in a 1:1 ratio into two parallel, controlled prophylaxis groups: fosfomycin or ciprofloxacin. The groups are stratified by site and by underlying disease (acute leukemia or stem cell transplantation).

FOVOCIP is a pragmatic study and very well adapted to the usual clinical practice of the sites of the public health system in Spain.

## Methods: participants, interventions, and outcomes

### Study setting {9}

The sponsor of this study is FINBA and plans to include 156 patients over 2 years; therefore, 11 Spanish national hospitals are needed to achieve the described objective.

The hospitals included are:✓ University Hospital Central of Asturias.✓ University Hospital La Paz.✓ University Clinic Hospital San Carlos.✓ Hospital San Pedro of Alcántara.✓ University Hospital Morales Messeguer.✓ University Hospital La Fe.✓ University Clinic Hospital of Valencia.✓ University Hospital of Málaga.✓ University Hospital Fundación Jiménez Díaz.✓ University Clinic Hospital Lozano Blesa.✓ University Hospital of Burgos.✓ These are academic hospital centers with experience in the management of acute leukemias and stem cell transplants. They are located around several regions in Spain. Therefore, they represent a broad spectrum of our country geography. This guarantees the representativeness of the Spanish population and the achievement of the planned recruitment.✓ The Clinical Trials agency and SCReN (Spanish Clinical Research Network) were responsible for obtaining authorization from the local ethics committee (EC) and notifying to the Spanish Agency of Medicines and Medical Devices of the start-up of the study.

### Eligibility criteria {10}

Candidate selection will be performed in 2 different settings depending on the therapeutic procedure:In subjects with a suspected diagnosis of acute leukemia, where the diagnosis of the neoplasm is made as an inpatient, the selection will take place once the diagnosis has been confirmed and prior to the start of intensive chemotherapy.In HSCT recipients, selection will take place on an outpatient basis during the pre-transplant evaluation.

**Inclusion criteria**

Subjects must meet all of the following inclusion criteria:

Subjects must be able to understand the study procedures, comply with them, and give written informed consent prior to any specific study procedure.Adult subjects 18 years of age who meet one of the following criteria:
Diagnosis of acute leukemia who are to receive a first course of intensive chemotherapy orCandidates to receive a first allogeneic hematopoietic progenitor transplant with myeloablative conditioning orCandidates to receive a first allogeneic hematopoietic progenitor transplant with reduced-intensity conditioning* or an autologous hematopoietic progenitor transplant provided that at least one of the following risk factors for infection is present: Performance status (Eastern Cooperative Oncology Group, ECOG) ≥ 2. Expected grade 3–4 mucositis. Age ≥ 65 years. Hematopoietic Comorbidity Transplant Index (HCTI) ≥ 3. Serum albumin < 35 g/L. Active or refractory neoplasia at the time of stem cell transplantation. Total dose of etoposide > 500 mg/m.^2^
 Total dose of cytarabine > 1 g/m.^2^

3.Performance status (Eastern Cooperative Oncology Group, ECOG) 0 to 3.4.Adequate organ function defined as:Liver: bilirubin, alkaline phosphatase, or SGOT < 3 times the upper limit of normal (unless attributable to tumor activity)Renal: creatinine ≤ 250 μmol/l (2.5 mg/dL) (unless attributable to leukemic infiltration)

5.Life expectancy greater than 3 months6.Women of childbearing age must not be pregnant or breastfeeding and must have a negative pregnancy test at the time of screening. Women of childbearing age and men with female partners of childbearing age must agree to practice 2 highly effective contraceptive measures and must agree not to become pregnant or father a child while receiving any study therapy and for at least 3 months after completion of treatment.

**Exclusion criteria**

Patients who meet any of the following exclusion criteria cannot be included in this study:

Hypersensitivity to fluoroquinolones or fosfomycin.Treatment with broad-spectrum antimicrobial therapy within 4 weeks of the first study treatment.Intensive chemotherapy or prior hematopoietic stem cell transplantation. Treatment with hydroxyurea or corticosteroids used to control white blood cell count is allowed.Fever of infectious origin or documented infection within 4 weeks of the first study treatment.Presence of any serious psychiatric illness or physical condition that, in the judgment of the physicians, contraindicates the patient’s inclusion in the clinical trial.

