## Statistical methods

### Statistical methods for primary and secondary outcomes {20a}

This phase 3 trial will compare the efficacy of fosfomycin with that of ciprofloxacin in preventing the occurrence of at least one episode of neutropenic fever of infectious origin in a randomized non-inferiority design.

The primary endpoint is febrile neutropenia of infectious origin. This analysis will be performed in the intention-to-treat (ITT) and in the per-protocol population (PP). The ITT population is defined as all patients who are eligible and randomized. The PP population consists of all patients who do not have major protocol deviations, as determined by the study PI, and have received prophylactic drugs for at least of 24 h.

The rate of febrile neutropenia will be compared between the 2 arms with a chi-square test with 2-sided alpha of 0.05. The difference in the proportion and the associated 95% CIs will be provided. If, within either patient arm, the data suggest a possible difference in baseline incidence between the randomization strata, we will consider Cochran-Mantel–Haenszel test to examine the association between the incidence of febrile neutropenia and the study treatment with adjustment for the randomization strata. Logistic regression models will be performed to evaluate the treatment effect on the incidence of febrile neutropenia adjusting for stratification and other baseline patient characteristics.

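### The exclusion for intensive chemotherapy is not limited by stratum and conflicts with the transplant inclusion criteria, leaving it unsettled which randomised transplant patients count as eligible in the primary analysis

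*Protocol article*

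**What the plan says.** The Exclusion criteria open with a rule for every candidate: "Patients who meet any of the following exclusion criteria cannot be included in this study". One item is "Intensive chemotherapy or prior hematopoietic stem cell transplantation". Its only exemption is "Treatment with hydroxyurea or corticosteroids used to control white blood cell count is allowed". It carries no time window, although another item in the list does: "Treatment with broad-spectrum antimicrobial therapy within 4 weeks of the first study treatment".

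The Inclusion criteria admit three kinds of patient:

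- Acute leukemia: "Diagnosis of acute leukemia who are to receive a first course of intensive chemotherapy".
- Candidates "to receive a first allogeneic hematopoietic progenitor transplant with myeloablative conditioning".
- Candidates for a first reduced-intensity allogeneic transplant or an autologous transplant who have at least one listed risk factor. One of the eight is "Active or refractory neoplasia at the time of stem cell transplantation".

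None of the transplant routes requires that the patient has had no intensive chemotherapy. The Objective (section {7}) joins intensively treated leukemia and transplant recipients with and/or. Section {16a} makes transplant one of the two disease strata.

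On analysis populations, section {20a} states: "The ITT population is defined as all patients who are eligible and randomized". Its PP set leaves out major protocol deviations as judged by the study PI. Section {20c} defines ITT as everyone randomised, in the allocated group. It defines PP only by at least 24 hours of the assigned treatment.

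**The concern.** A patient can satisfy the Inclusion criteria as a transplant candidate and fail the Exclusion criteria because of earlier treatment of the same malignancy. A leukemia patient who had intensive induction and then comes to a first allogeneic transplant is the plain case.

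Two things are at stake. First, eleven sites may apply the item differently, so the make-up of the transplant stratum would depend on local interpretation. Second, the eligibility question reaches the primary analysis. Under {20a}, an ineligible patient is outside ITT and may be called a major deviation for PP. Section {23} has monitors check all selection criteria, so a literal reading would be recorded as deviations. The trial is open-label and investigators know the allocation (section {17a}). A unclear criterion settled case by case after randomisation would therefore leave room for judgement made with knowledge of arm and outcome. A uniform rule based on a baseline fact would not.

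**Working it through.** The point concerns wording and disputes no figure in the plan. The check sets the texts side by side.

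**Step 1. What the item can mean.** The word prior stands only before the transplant term.

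- If it does not also govern intensive chemotherapy, the item bars the leukemia patients who are enrolled to receive exactly that. This reading is unworkable.
- If it does, the item bars anyone with earlier intensive chemotherapy. This fits the leukemia route (a first course) and the exemption for white-cell control. It is the only workable reading.

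**Step 2. Whom that reading reaches.** The list applies to all candidates, and no section exempts transplant candidates.

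| Route | Inclusion text on earlier treatment | Effect of the exclusion |
|---|---|---|
| Acute leukemia | first intensive course | consistent |
| Myeloablative allogeneic | first allogeneic transplant; silent on chemotherapy | bars those previously given intensive chemotherapy |
| Reduced-intensity allogeneic or autologous | as above for reduced-intensity; refractory disease can qualify | bars those previously given intensive chemotherapy |

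Refractory disease implies earlier treatment. Listing active disease as an added risk suggests that other candidates are in remission. The and/or in the Objective foresees patients with both treatments.

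**Step 3. How many.** The protocol gives neither the transplant share *h* nor the share *q* of those patients with earlier intensive chemotherapy. Both are assumptions here. Affected patients = 156 × *h* × *q*.

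- Low (*h* = 0.30, *q* = 0.25): 156 × 0.075 = 11.7, about 12.
- Middle (*h* = 0.50, *q* = 0.50): 156 × 0.25 = 39.
- High (*h* = 0.70, *q* = 0.90): 156 × 0.63 = 98.3, about 98.

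For scale, the Sample size section leaves 156 − 134 = 22 patients for all ineligible or non-evaluable cases. The assumed range runs from below that allowance to far above it.

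**Step 4. What follows in the analysis.**

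| Section | ITT | PP |
|---|---|---|
| {20a} | eligible and randomised: affected patients could be removed | major deviations removed, as judged by the study PI: could be removed |
| {20c} | all randomised: affected patients stay | 24 hours of assigned drug: affected patients stay |

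The protocol therefore supports both outcomes for the same patient.

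**The case against.** The strongest reply is that this is a condensed line in a journal article. The first-course wording and the hydroxyurea exemption suggest a criterion drafted for newly diagnosed leukemia. The full protocol may define intensive chemotherapy, which the article does not. No section says that transplant candidates have had such treatment. Refractory disease implies some earlier therapy, not necessarily intensive chemotherapy, and that risk factor does not apply to the myeloablative route. This stands as a limit on how far the conflict reaches. It does not remove the conflict, because the article states a rule for all patients and gives no exemption.

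A reader might go further and infer that the transplant stratum cannot be filled, or that half of the target population is shut out. The documents support neither. Transplant candidates without earlier intensive chemotherapy remain eligible, and no stratum sizes are given.

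A reader might also infer a definite loss of power. That does not follow. If affected patients are simply not enrolled, other eligible patients can make up the 156, since no stratum quota is stated. Power falls only if randomised patients are later removed, and {20c} says that they are not. Any power figure would also rest on an unstated stratum size and on the sidedness of alpha, which is a separate question.

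**Conclusion.** The conflict holds. The exclusion, in its only workable reading, contradicts the transplant inclusion criteria and the stated target population, and it makes an unquantified part of the transplant stratum ineligible. The range of about 12 to 98 of 156 is an illustration under assumed shares, not an estimate; the conflict does not depend on it.

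The consequence for the primary analysis is conditional. It arises if the criterion is read literally, if sites have nevertheless randomised such patients, and if the {20a} populations are used instead of those in {20c}. The Trial status section reports 106 patients recruited but gives no breakdown by stratum or earlier treatment, so it cannot be said whether any are affected. This is a defect of wording that is cheap to repair and worth settling before the data are analysed.

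**What to change.** 1. The sponsor should reconcile the Objective, the Inclusion criteria and the Exclusion criteria by amendment. The amendment should state whether the exclusion for earlier intensive chemotherapy applies, to which stratum, and what counts as intensive. Which eligibility rule is right is for the sponsor to decide.
2. Use the all-randomised definition in {20c} as the single ITT definition and correct {20a} to match. No randomised transplant patient is then dropped from ITT because of this criterion.
3. Before analysis, fix in writing how randomised transplant patients with earlier intensive chemotherapy are classified for PP. Decide this blind to arm, as one rule for all such patients, and align the PP definitions in {20a} and {20c}. Report the number of such patients by arm.

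The cost is a short amendment, its notification to the agency and the ethics committee under section {25}, and a review of earlier treatment in the transplant patients already randomised. No sample size figure changes.

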### Who will take informed consent? {26a}

Principal investigators in each site will provide informed consent to patient candidates for participation. The latest version approved of the patient’s information sheet will be signed by all selected subjects before inclusion in the clinical trial.

In the case of selected subjects who cannot understand the study or do not have the ability to read or write, the informed consent must be provided by the legal representative before any procedure of the study is carried out.

### Additional consent provisions for collection and use of participant data and biological specimens {26b}

This study complies with the current regulations of Law 14/2007 on biomedical research regarding the protection of the rights of patients who freely wish to participate and the handling of biological samples.

No biological samples from patients will be stored after the end of the clinical trial.

## Interventions

### Explanation for the choice of comparators {6b}

#### Intervention description {11a}

The description of the interventions and comparators is detailed in Table 1.

**Table 1 Tab1:** Intervention description

Groups	Interventions
Experimental group	Patients in this arm will receive study medication fosfomycin 500 mg every 8 h orally or intravenously in case of intolerance to the oral route
Control group	Ciprofloxacin 500 mg every 12 h orally or intravenously in case of intolerance to the oral route (https://clinicaltrials.gov/study/NCT01371656?term=ACCL0934&rank=1)

### Criteria for discontinuing or modifying allocated interventions {11b}

Treatment will be interrupted when any of the following events occurs first:

Febrile neutropenia requiring antibacterial treatment (main end point of the study).Absolute neutrophil count (ANC) > 0.5 × 10^9^/L.If the subject fails to achieve more than 0.5 × 10^9^/L neutrophils, treatment will end when more than 60 days have elapsed since the onset of neutropenia or on the first day of the next chemotherapy cycle (whichever occurs first).Death

